### III. Detailed description of research activities

#### 1. Research abstract

##### 1.1 Abstract

**Research name:** A randomized controlled trial for the long-term outcomes of MMF on new onset SLE patients with high titers of anti-dsDNA antibody for reducing main organ involvement

**Research Introduction:** Systemic lupus erythematosus (SLE) is an autoimmune disease that can affect multiple organs. The abnormality of the immune system is manifested by the existence of a large number of circulating self-antigens in the body, resulting in the production of autoantibodies against various self-antigens and causing immune damage to organs. Among them, anti-dsDNA antibodies are the most important autoantibodies, and high titers of anti-dsDNA antibodies are closely related to the pathogenesis of lupus nephritis, and can cause damage to other multiple organs, such as liver, heart, and lungs. Studies have shown that the incidence of SLE in the Asian population is about 8.4/100,000 people/year, and severe cases can even be life-threatening, bringing a significant economic burden to people's lives and economy. As a commonly used immunosuppressant, mycophenolate mofetil (MMF) has been widely used for induction and maintenance of lupus nephritis, and also plays an important role in the treatment of other extra-renal organ damage. Therefore, we propose the scientific hypothesis that whether early application of MMF to newly diagnosed SLE patients with high titer of anti-dsDNA antibody and without major organ involvement could improve the long-term prognosis.

In this study, new-onset SLE patients were screened. Participants who met the inclusion criteria were randomly assigned (1:1) by the Department of Rheumatology and Immunology of Ruijin hospital to receive either MMF (MMF group) or control (Control group). Control group received treatment with HCQ (5mg/kg/day) and prednisone (0.5mg/kg/day); while MMF group received treatment with HCQ (5mg/kg/day) and prednisone (0.5mg/kg/day) plus MMF 500mg twice daily. The first follow-up of treatment was week 24, and then every 24 weeks for a total of 96 weeks. The primary endpoint was the proportion of SLE patients having flares (mild-to-moderate

flare and severe flare) according to SELENA-SLEDAI Flare Index. The secondary endpoints included: 1) the proportion of lupus low disease activity state (LLDAS) at week 96; 2) short form-36 (SF-36) score before and after treatment; 3) the proportion of adverse events in the two groups during follow-up; 4) changes in SLEDAI-2000 score; 5) changes in prednisone dose. This study is of great importance to improve the level of diagnosis and treatment in this field in China, and to promote Chinese clinical research results to the world, even into clinical guidelines, and to improve the academic level and status of China.

**Research purposes:**

This project mainly investigates whether early application of MMF to newly diagnosed SLE patients with high titer of anti-dsDNA antibody and without major organ involvement could improve the long-term prognosis.

Objective 1: The proportion of SLE patients having flares (mild-to-moderate flare and severe flare) according to SELENA-SLEDAI Flare Index.

Objective 2:

- 1) The proportion of lupus low disease activity state (LLDAS) at week 96;
- 2) Short form-36 (SF-36) score before and after treatment;
- 3) The proportion of adverse events in the two groups during follow-ups;
- 4) Changes in SLEDAI-2000 score;
- 5) Changes in prednisone dose.

**Research objects:**

A total of 130 people were enrolled, and they were randomly divided into the experimental group and the control group at a 1:1 ratio by randomization, with 65 cases in each group.

During enrolment, patients were required:

Inclusion Criteria:

- 1) Age between 18 and 65 years old;
- 2) Diagnosed with SLE at the time of screening by fulfilling ACR 2019 classified criteria or its 2017 version;
- 3) Have not received any prior SLE treatment;
- 4) Have a positive antinuclear antibody (HEp-2 titer  $\geq 1:80$ );
- 5) Have a positive anti-dsDNA antibody (fulfilled both anti-dsDNA (ELISA)  $\geq 300$  IU/mL and anti-dsDNA (CLFT)  $\geq 1:10$ );
- 6) Do not have major organ involvement (i.e., brain, heart, liver, kidney, lung, muscle, serous cavity and gastrointestinal tract).

Participants were permitted to have rash, arthritis, alopecia, oral ulcer, and mild hematologic system involvement (white blood cell  $>1.5 \times 10^9/L$  and  $<4 \times 10^9/L$ , hemoglobin  $>90g/L$  and  $<120g/L$ ,

platelet  $>60 \times 10^9/L$  and  $<100 \times 10^9/L$ ).

Exclusion Criteria:

- 1) SLE patients who had been treated,
- 2) Liver and kidney dysfunction (Alanine aminotransferase (ALT)/ aspartate aminotransferase (AST)  $> 2$  times upper normal limits; creatinine clearance rate  $< 60\text{ml/min}$ ),
- 3) Cancer,
- 4) Recent infection or hematologic diseases not caused by SLE,
- 5) Pregnancy or planned to be pregnant,
- 6) Patients not willing to join the study.

**Research center/Location:** Ruijin Hospital, Shanghai Jiao Tong University School of Medicine; The First Affiliated Hospital of Wenzhou Medical University, Wenzhou Medical University; The Second Affiliated Hospital of Shandong First Medical University, Shandong First Medical University.

**Research Interventions:** In this study, new-onset SLE patients were screened. Participants who met the inclusion criteria were randomly assigned (1:1) by the Department of Rheumatology and Immunology of Ruijin hospital to receive either MMF (MMF group) or control (Control group). Control group received treatment with HCQ (5mg/kg/day) and prednisone (0.5mg/kg/day); while MMF group received treatment with HCQ (5mg/kg/day) and prednisone (0.5mg/kg/day) plus MMF 500mg twice daily. The first follow-up of treatment was at week 24, and then every 24 weeks for a total of 96 weeks. The primary endpoint was the proportion of SLE patients having flares (mild-to-moderate flare and severe flare) according to SELENA-SLEDAI Flare Index. The secondary endpoints included: 1) The proportion of lupus low disease activity state (LLDAS) at week 96; 2) Short form-36 (SF-36) score before and after treatment; 3) The proportion of adverse events in the two groups during follow-up; 4) Changes in SLEDAI-2000 score; 5) Changes in prednisone dose.

**Study Duration:** September 2018 to September 2021

**Subject participation time:** 96 weeks per subject from screening enrollment to completion of all follow-up visits

## 1.2 Workflow

[figure not shown]

## **2. Research Background**

### **2.1 Research Significance**

This research will investigate the long-term prognosis and impact on organs in newly diagnosed SLE patients with high titer of anti-dsDNA antibody and without major organ involvement, in a randomized controlled trial with or without MMF. This research is important to improve the treatment in this field.

### **2.2 Research Background**

Systemic lupus erythematosus (SLE) is an autoimmune disease that can affect multiple organs in the body, and is known as the prototype of autoimmune disease. The abnormality of the immune system is manifested by the existence of a large number of circulating self-antigens in the body, resulting in the production of a large number of autoantibodies against various self-antigens and causing immune damage to organs. Research shows that the incidence in Asian population is about 8.4/100,000 people/year. SLE can affect multiple systems in the body, such as kidney, heart, and lung. In severe cases, it can be life-threatening and bring a significant economic burden to people's lives and economy. The current 10-year mortality rate of SLE patients in China reaches 20%. Therefore, early treatment of patients is particularly important. Evidence from clinical studies has revealed that many autoantibodies can appear earlier than the onset of the disease, and it has been reported that many autoantibodies, such as anti-nuclear, anti-dsDNA, and anti-Sm antibodies, can be detected in the serum of patients before the diagnosis of SLE disease, even 5 years before the first symptoms of SLE. To date, hundreds of autoantibodies have been detected in SLE patients, most of which are useful in the diagnosis of the disease, and some of which are pathogenic and associated with lupus nephritis, such as anti-dsDNA and anti-C1q antibodies. The prevalence of nephritis in patients with high titers of anti-dsDNA antibodies was 30.2%, compared with only 18.7% in negative patients. Anti-dsDNA antibodies are an independent risk factor for SLE disease activity score (SLEDAI score) greater than 5, which can lead to nephritis, arthritis and serositis. Because patients who are not treated in the early stage of the disease often lead to multi-organ damage, even if they are actively treated in the late stage of the disease, they still cause irreversible severe consequences. Glucocorticoids use can reduce disease relapse in SLE patients with high titers of anti-dsDNA antibodies. Glucocorticoids can reduce the expression of cytokines and adhesion molecules, inhibiting the tendency of leukocytes to enter sites of inflammation, and interfering with leukocyte, fibroblast, and endothelial cells. Glucocorticoids reduce the expression of MHC and Fc receptors and the synthesis of pro-inflammatory cytokines such as IL-2, IL-6, and TNF- $\alpha$ . Glucocorticoids also have an effect on T cells, reducing the production and action of IL-2 and the total number of circulating T cells. In addition, glucocorticoids also affect fibroblast function by decreasing vascular permeability, expression of adhesion molecules and IL-1 production. Finally, glucocorticoids affect fibroblast function by reducing fibroblast proliferation and the production of fibronectin and prostaglandins. This lead to the decline of the body's ability to resist infection, resulting in increased mortality, with prednisone  $\leq 5$  mg/d associated with

infection risk of 1.1 and greater than 20 mg/d associated with infection risk of 1.85. Other side effects of glucocorticoids include increased blood glucose, blood pressure and osteoporosis. The advent of immunosuppressants has reduced the use of glucocorticoids and improved the survival rate of SLE patients. Mycophenolate mofetil (MMF) has been widely used as a commonly used immunosuppressant to induce remission and as a maintenance drug in lupus nephritis. MMF selectively inhibits the classical guanine synthesis pathway in lymphocytes by reversibly inhibiting hypoxanthine mononucleotide dehydrogenase without affecting the purine remediation synthesis pathway. Lymphocytes only have the classical synthesis pathway, but not the remediation synthesis pathway, so MMF can selectively inhibits lymphocyte proliferation by inhibiting the lymphocyte growth cycle, T cell and B cell proliferation and antibody production, as well as inhibiting glycoprotein conversion, reducing adhesion factor activity, inhibiting vascular smooth muscle cell proliferation and macrophage accumulation. MMF is also effective in active SLE with extra-renal involvement and can lead to a reduction in the use of glucocorticoids. The international expert group on SLE has identified key issues for future research in SLE, among which early treatment of SLE patients is one of the hot topics. Although MMF can be useful for controlling disease activity, interventions that begin in the early stages of SLE before systemic involvement have not been reported. Whether the addition of early treatment with MMF in new onset SLE patients with high titers of anti-dsDNA antibodies but without systemic involvement can improve the long-term prognosis and reduce disease flare remains to be investigated.

In conclusion, this research explores the long-term prognosis and impact on target organs in newly diagnosed SLE patients with high titer of anti-dsDNA antibodies but without major organ involvement.

### **2.3 Expected Outcomes of the Research**

This randomized controlled trial was conducted to investigate the need for early treatment in newly diagnosed SLE patients with high titer of anti-dsDNA antibody and without major organ involvement. One SCI paper is expected to be completed.

### **2.4 Risk/Benefit Assessment**

#### **2.4.1 Potential risks**

Currently, mycophenolate mofetil and glucocorticoids are used as first-line drugs in systemic lupus erythematosus. The research has no psychological harm, no financial loss and no legal harm to the patients. No pain and bodily harm. During treatment, patients may develop infection due to the use of glucocorticoids and immunosuppressants, as well as gastrointestinal reactions and blood counts that may be influenced by mycophenolate mofetil.

#### **2.4.2 Known potential benefit**

The social benefits of this research may be to improve the prognosis of patients with new-onset SLE. The benefit to individual subject lies in the early control of disease progression, which may be helpful for the long-term prognosis of patients.

#### **2.4.3 Potential Risk/Benefit Assessment**

Currently, mycophenolate mofetil and glucocorticoids are used as first-line drugs in systemic lupus erythematosus. The study has no psychological harm, no financial loss and no legal harm to the patients. No pain and bodily harm. Both glucocorticoids and immunosuppressants have the risk of causing infection. The side effects of the drug can be monitored, and if the infection occurs, anti-infective treatment can also be administered in the hospital.

#### 4. Research objectives

This project investigates whether early application of MMF to newly diagnosed SLE patients with high titer of anti-dsDNA antibody and without major organ involvement could improve the long-term prognosis.

Objective 1: The proportion of SLE patients having flares (mild-to-moderate flare and severe flare) according to SELENA-SLEDAI Flare Index.

Objective 2:

- 1) The proportion of lupus low disease activity state (LLDAS) at week 96;
- 2) Short form-36 (SF-36) score before and after treatment;
- 3) The proportion of adverse events in the two groups during follow-ups;
- 4) Changes in SLEDAI-2000 score;
- 5) Changes in prednisone dose.

The primary outcome was the proportion of patients who have flares (mild-to-moderate flares and severe flares) defined by modified SELENA-SLEDAI Flare Index (SFI) at 96 weeks of

follow-up.

Secondary Endpoints:

- 1) The proportion of lupus low disease activity state (LLDAS) at week 96;
- 2) Short form-36 (SF-36) score of before and after treatment in two groups;
- 3) The proportion of adverse events of two groups in the follow-ups;
- 4) Changes in SLEDAI-2000 score;
- 5) Changes in prednisone dose.

## **5. Research design**

### **5.1 General design**

This research is a randomized clinical trial with 65 patients in each group calculated according to the PASS 11.0 software. In this trial, new-onset SLE patients were screened. Participants who met the inclusion criteria were randomly assigned (1:1) to receive either MMF (MMF group) or control (Control group). Control group received treatment with HCQ (5mg/kg/day) and prednisone (0.5mg/kg/day); while MMF group received treatment with HCQ (5mg/kg/day) and prednisone (0.5mg/kg/day) plus MMF 500mg twice daily. The first follow-up of treatment was at week 24, and then every 24 weeks for a total of 96 weeks. The primary endpoint was the proportion of SLE patients having flares (mild-to-moderate flare and severe flare) according to SELENA-SLEDAI Flare Index. The secondary endpoints included: 1) The proportion of lupus low disease activity state (LLDAS) at week 96; 2) Short form-36 (SF-36) score before and after treatment; 3) The proportion of adverse events in the two groups during follow-up; 4) Changes in SLEDAI-2000 score; 5) Changes in prednisone dose.

### **5.2 Define research endpoints**

The primary endpoint was the proportion of SLE patients having flares (mild-to-moderate flare and severe flare) according to SELENA-SLEDAI Flare Index. The secondary endpoints included: 1) The proportion of lupus low disease activity state (LLDAS) at week 96; 2) Short form-36 (SF-36) score before and after treatment; 3) The proportion of adverse events in the two groups during follow-up; 4) Changes in SLEDAI-2000 score; 5) Changes in prednisone dose.

### 5.3 Determining sample size

We referred to the flare rate of the placebo arm in ‘Met Lupus’ trial and the flare rate from the BLISS-52, BLISS-76 and BLISS-North East Asia phase III trials. We supposed the flare rate to be 10% in MMF group and 30% in Control group. Z test with unpooled variance (alpha=0.0568, beta=0.1964, power=0.8036) was used for sample size calculation. A sample size of 58 patients per group would provide the trial with 80% power at a two-sided alpha error of 0.05 to detect a difference between the two groups using the software PASS version 11.0. Taking an estimated 10% drop-out into account, a sample size of 65 patients per group could fulfill the statistical requirement. The sample size was calculated using PASS version 11.0 software as follows:

Two Independent Proportions (Null Case) Power Analysis  
Numeric Results of Tests Based on the Difference: P1 - P2  
H0: P1-P2=0. H1: P1-P2=D1<>0. Test Statistic: Z test with unpooled variance

|       | Sample
Size
Grp 1
N1 | Sample
Size
Grp 2
N2 | Prop H1
Grp 1 or
Trtmnt
P1 | Prop
Grp 2 or
Control
P2 | Diff
if H0
D0 | Diff
if H1
D1 | Target
Alpha | Actual
Alpha | Beta   |
|-------|-------------------------------|-------------------------------|-------------------------------------|-----------------------------------|---------------------|---------------------|-----------------|-----------------|--------|
| Power | 58                            | 58                            | 0.1000                              | 0.3000                            | 0.0000              | -0.2000             | 0.0500          | 0.0568          | 0.1964 |

Reference:

## 6. Research object

### 6.1 Inclusion criteria

- 1) Age between 18 and 65 years old;
- 2) Diagnosed with SLE at the time of screening by fulfilling ACR 2019 classified criteria or its 2017 version;
- 3) Have not received any prior SLE treatment;
- 4) Have a positive antinuclear antibody (HEp-2 titer  $\geq 1:80$ );
- 5) Have a positive anti-dsDNA antibody (fulfilled both anti-dsDNA (ELISA)  $\geq 300$  IU/mL and anti-dsDNA (CLFT)  $\geq 1:10$ );
- 6) Do not have major organ involvement (i.e., brain, heart, liver, kidney, lung, muscle, serous cavity and gastrointestinal tract). Participants were permitted to have rash, arthritis, alopecia,

oral ulcer, and mild hematologic system involvement (white blood cell  $>1.5 \times 10^9/L$  and  $<4 \times 10^9/L$ , hemoglobin  $>90g/L$  and  $<120g/L$ , platelet  $>60 \times 10^9/L$  and  $<100 \times 10^9/L$ ).

## **6.2 Exclusion criteria**

- 1) SLE patients who had been treated;
- 2) Liver and kidney dysfunction (Alanine aminotransferase (ALT)/ aspartate aminotransferase (AST)  $> 2$  times upper normal limits; creatinine clearance rate  $< 60ml/min$ );
- 3) Cancer;
- 4) Recent infection or hematologic diseases not caused by SLE;
- 5) Pregnancy or planned to be pregnant;
- 6) Patients not willing to join the study.

## **6.3 Things to pay attention to in life**

None

## **6.4 Recruitment of patients**

We referred to the flare rate of the placebo arm in 'Met Lupus' trial and the flare rate from the BLISS-52, BLISS-76 and BLISS-North East Asia phase III trials. We supposed the flare rate to be 10% in MMF group and 30% in Control group. Z test with unpooled variance ( $\alpha=0.0568$ ,  $\beta=0.1964$ ,  $\text{power}=0.8036$ ) was used for sample size calculation. A sample size of 58 patients per group would provide the trial with 80% power at a two-sided alpha error of 0.05 to detect a difference between the two groups using the software PASS version 11.0. Taking an estimated 10% drop-out into account, a sample size of 65 patients per group could fulfill the statistical requirement.

Recruit patients according to the inclusion and exclusion criteria:

Inclusion Criteria:

- 1) Age between 18 and 65 years old;
- 2) Diagnosed with SLE at the time of screening by fulfilling ACR 2019 classified criteria or its 2017 version;
- 3) Have not received any prior SLE treatment;
- 4) Have a positive antinuclear antibody (HEp-2 titer  $\geq 1:80$ );
- 5) Have a positive anti-dsDNA antibody (fulfilled both anti-dsDNA (ELISA)  $\geq 300 IU/mL$  and anti-dsDNA (CLFT)  $\geq 1:10$ );
- 6) Do not have major organ involvement (i.e., brain, heart, liver, kidney, lung, muscle, serous cavity and gastrointestinal tract). Participants were permitted to have rash, arthritis, alopecia, oral ulcer, and mild hematologic system involvement (white blood cell  $>1.5 \times 10^9/L$  and  $<4 \times 10^9/L$ , hemoglobin  $>90g/L$  and  $<120g/L$ , platelet  $>60 \times 10^9/L$  and  $<100 \times 10^9/L$ ).

Exclusion Criteria:

- 1) SLE patients who had been treated ;
- 2) Liver and kidney dysfunction (Alanine aminotransferase (ALT)/ aspartate aminotransferase (AST)  $> 2$  times upper normal limits; creatinine clearance rate  $< 60ml/min$ );
- 3) Cancer ;
- 4) Recent infection or hematologic diseases not caused by SLE, ;
- 5) Pregnancy or planned to be pregnant, ;
- 6) Patients not willing to join the study.

Control and grouping: computerized randomization method was used. Grouping was divided into Control and MMF group. Each patient signed an informed consent form before enrollment and the physician was obliged to answer the patient's questions during the follow-up, and the patient had the right to withdraw from the study at any time. Patients have the right to give consent if treatment changes occur.

Research centers:

Ruijin Hospital Affiliated to Shanghai Jiaotong University School of Medicine; The First Affiliated Hospital of Wenzhou Medical University; The Second Affiliated Hospital of Shandong First Medical University

Number of study subjects: 130 cases

Recruitment location: the above three hospitals

Measures to strengthen the compliance of research subjects: regularly follow up reminders to the patients.

## **6.5 Methods of subject assignment**

Participants were randomly assigned (1:1) using blocks of four to receive either MMF (MMF group) or a control treatment (Control group). A statistician from the Clinical Trial Center of Ruijin Hospital, [name], who was masked to trial allocation generated the randomization sequences by a computer algorithm. Then, random numbers were written on the cards and packed in sequentially numbered envelopes that were opened when the patients were enrolled. [name] assigned patients to different groups according to the number on the card. Only Assessors were masked to the group allocation. Eligible subjects were recruited from the Department of Rheumatology and Immunology of Ruijin Hospital and the Department of Rheumatology and Immunology of the other two clinical centers.

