| STUDY DESIGN                        | Multicenter randomized clinical trial                                                                                                                                                                                                                                                                                                                                                                                                                                                                                                                                                                                                                                                                                                                                                                                                                                                                                                                                                                                                                                                                                                                                                                                                                                                                                                             |

In this study, new-onset SLE patients were screened. Participants who met the inclusion criteria were randomly assigned (1:1) by the Department of Rheumatology and Immunology of Ruijin hospital to receive either MMF (MMF group) or control (Control group). Control group received treatment with HCQ (5mg/kg/day) and prednisone (0.5mg/kg/day); while MMF group received treatment with HCQ (5mg/kg/day) and prednisone (0.5mg/kg/day) plus MMF 500mg twice daily. The first follow-up of treatment was week 24, and then every 24 weeks for a total of 96 weeks. The primary endpoint was the proportion of SLE patients having flares (mild-to-moderate flare and severe flare) according to SELENA-SLEDAI Flare Index. The secondary endpoints included: 1) the proportion of lupus low disease activity state (LLDAS) at week 96; 2) short form-36 (SF-36) score before and after treatment; 3) the proportion of adverse events in the two groups during follow-up; 4) changes in SLEDAI-2000 score; 5) changes in prednisone dose.

**INCLUSION  
CRITERIA**

During enrolment, patients were required:

Inclusion Criteria:

- 1) Age between 18 and 65 years old;

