### 7.3 Measures to reduce bias: randomization and blinding

Participants were randomly assigned (1:1) using blocks of four to receive either MMF (MMF group) or a control treatment (Control group). A statistician from the Clinical Trial Center of Ruijin Hospital, [name], who was masked to trial allocation generated the randomization sequences by a computer algorithm. Then, random numbers were written on the cards and packed in sequentially numbered envelopes that were opened when the patients were enrolled in the trial. They were assigned to the trial group according to the number on the card. Eligible subjects were recruited from the Department of Rheumatology and Immunology of Ruijin hospital and Department of Rheumatology and Immunology of the other two clinical centers. [name] randomly assigned patients to different groups according to number sequence. Assessors were masked to the group allocation. Observers were masked to the group allocation and they were responsible for regular follow-up assessments. Data analysts ([name] and [name]) were not involved in patient assessment and treatment, and they were masked to the group allocation.

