## **8. Statistical procedures**

### **8.1 Randomization and masking**

Participants were randomly assigned (1:1) using blocks of four to receive either MMF (MMF group) or a control treatment (Control group). A statistician from the Clinical Trial Center of Ruijin Hospital, [name], who was masked to trial allocation generated the randomization sequences by a computer algorithm. Then, numbers were written on the cards and packed in sequentially numbered envelopes that were opened when the patients were enrolled. [name] assigned patients to different groups according to the number on the card. Assessors were masked to the group allocation. Eligible subjects were recruited from the Department of Rheumatology and Immunology of Ruijin Hospital and the Department of Rheumatology and Immunology of the other two clinical centers. Doctors were responsible for patient inclusion and regular follow-up assessments ([name], [name], [name], [name], and [name]). The assessment of patient flare was strictly based on the SELENA-SLEDAI Flare Index (including severe flare, and mild to moderate flare) rather than subjective decisions. Data analysts ([name] and [name]) were not involved in patient assessment and treatment, and they were masked to the group allocation.

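### A single fixed block size of four in an open-label trial lets part of the allocation sequence be deduced, and the list structure and recruiter masking that decide how much are not settled

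*Combined protocol and SAP*

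**What the plan says.** Protocol 6.5 states: "Participants were randomly assigned (1:1) using blocks of four to receive either MMF (MMF group) or a control treatment (Control group"). Protocol 7.3 and SAP 8.1 repeat the rule. None of the three describes varied block sizes, stratification by centre, or withholding the block size from recruiters.

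A statistician at the sponsor hospital's trial centre generates the sequence by computer. The numbers go on cards, "packed in sequentially numbered envelopes that were opened when the patients were enrolled". The envelopes are not described as sealed or opaque.

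On who assigns, the protocol Summary has patients "randomly assigned (1:1) by the Department of Rheumatology and Immunology of Ruijin hospital", while 6.5 and SAP 8.1 give the task to one named person. Protocol 6.4 gives "Recruitment location: the above three hospitals" and "Number of study subjects: 130 cases". Whether there is one list or one per centre is not stated.

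Treatment is open. The protocol's brief list marks placebo as not used, 7.1.3 declares unblinding codes not applicable, and under 7.2.1 patients buy the drugs on the doctor's prescription.

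The documents say three things about masking:
- Protocol 6.5: "Only Assessors were masked to the group allocation".
- Protocol 7.3: "Observers were masked to the group allocation and they were responsible for regular follow-up assessments".
- SAP 8.1: assessors are masked, and also "Doctors were responsible for patient inclusion and regular follow-up assessments".

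**The concern.** With a fixed block of four, the last allocation in every block is forced, and the third is forced whenever the first two match. Envelopes hide the next card, but they do not help if its content can be worked out from the cards already opened. In an open-label trial, whoever treats earlier patients knows their arm.

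Eligibility leaves some room for discretion. Absence of major organ involvement and recent infection both need judgement, and enrolment can be delayed by a few days. A recruiter who knows the next arm could, deliberately or not, place patients of higher or lower flare risk in it. That would bias the primary comparison of flare proportions. SAP 8.5 contains no analysis that would look for it.

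**Working it through.** **The plan's own figures.** The documents give no figure for predictability. The yardstick is the planned flare difference of 30% against 10%, or 20 points (protocol 5.3, SAP 6). That calculation reproduces: exact enumeration of the unpooled Z test at 58 per group gives power 0.8036 and actual alpha 0.0568, and 58/0.9 = 64.4, rounded up to 65.

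**Full knowledge (block size, block starts and all earlier allocations known).** A block of four has 6 balanced sequences.
- The fourth allocation is always determined. The third is determined when the first two match, in 2 of 6 sequences.
- Mean determined share = (1 + 1/3)/4 = 33.3%.
- Range within a block: 1/4 = 25% to 2/4 = 50%.
- Correct guesses by position: 1/2, 2/3, 2/3, 1. Mean = (1/2 + 2/3 + 2/3 + 1)/4 = 17/24 = 70.8%; chance is 50%.
- For 130 patients: 130/4 = 32.5, so 32 full blocks plus 2 patients. Expected determined = 32 × 4/3 = 42.7, or 42.7/130 = 32.8%. In simulation the 95% range is 38 to 48, and about 37% of lists exceed one third.

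**One list shared by three centres, each recruiter seeing only their own centre (assumption; envelope numbers known).** A slot is determined only if the two earlier patients who share an arm were both at the recruiter's centre. With centre shares w, the determined share is (1/3) × Σw³.

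| Centre split (assumed) | Σw³ | Determined | Correct guesses |
|---|---|---|---|
| 80/10/10 | 0.514 | 17% | 63% |
| 60/20/20 | 0.232 | 8% | 59% |
| equal | 0.111 | 4% | 57% |

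**Randomly varied sizes 4, 6 and 8, unknown to the recruiter (simulation, all earlier allocations seen).** Determined share is about 2.4% and correct guessing about 68%. The excess over chance falls only from 20.8 to 18 points.

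**Possible bias.** Suppose steering acts only on determined slots. Let d be the difference in mean flare risk between patients placed in determined control slots and those placed in determined MMF slots. The resulting difference between arms is share × d. The documents give no value for d; I assume 0 to 20 points.
- d = 0: no bias under any list structure.
- Full knowledge: 0.333 × 10 = 3.3 points; 0.333 × 20 = 6.7 points.
- Shared list: 0.04 × 10 = 0.4 points; 0.17 × 20 = 3.4 points.

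**Timing.** The protocol Summary ends the study in September 2021 with 96 weeks per subject. Counting 96 weeks back from 30 September 2021 gives 28 November 2019. Version 2.0 is dated 9 August 2020, so on these dates enrolment had closed.

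**The case against.** A reader might infer four stronger claims. The documents do not support them.

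- **That the recruiting doctors are unmasked.** Protocol 6.5 can be read that way. But protocol 7.3 masks those who do follow-up assessments, and SAP 8.1 gives inclusion and follow-up to the same doctors, which would make the recruiters the masked assessors. Recruiters truly masked to earlier allocations could not deduce the next. The passages conflict and settle neither reading. No procedure is described that would keep recruiters from learning earlier allocations.
- **That one third is a ceiling.** It is a mean under full knowledge. A block can give half, and a shared list can give far less.
- **That the block size was public during recruitment.** Protocol 11.7 releases the protocol only on publication of results, on request. Exposure would be limited to staff who held it.
- **That the recruiting department itself ran the allocation.** The Summary names a department, but 6.5 and SAP 8.1 name one person. Overlap with the recruiters cannot be judged.

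Real concealment elements exist: a computer-generated sequence, a separate statistician, and numbered envelopes opened only at enrolment. The blood-count and anti-dsDNA limits are numeric, so discretion is narrower than it first appears. Varied block sizes reduce certainty far more than they reduce informed guessing. Rewriting the block rule after enrolment would misreport what was done.

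All of this stands, and it limits the size of the concern and the choice of remedy. It does not remove the point: a single fixed block size in an open-label trial, with no stated safeguard against deduction and no analysis that checks for its effect.

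**Conclusion.** The concern holds as a design weakness of uncertain size. Under full knowledge of earlier allocations, one third of allocations are determined on average and about 71% can be guessed. Under a shared list with recruiters seeing only their own centre, the determined share is about 4% to 17%. Which applies depends on list structure and masking, neither of which the documents settle.

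The possible bias in the flare difference runs from zero to a few points (at most 6.7 under the assumptions above), against a planned difference of 20. Nothing in the documents shows that any allocation was predicted or any patient steered. The remedy is cheap and worth adopting.

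**What to change.** 1. **Reconcile the text.** Make protocol 6.5 and 7.3 and SAP 8.1 agree on whether the doctors who include patients were masked. State whether there was one list or one per centre, who saw earlier allocations, and whether envelopes were sealed and opaque. Cost: a few sentences.
2. **If any allocation remains,** generate it with randomly varied block sizes (for example 4, 6 and 8), held by the statistician in a restricted file and not printed in the protocol. Cost: a small change to the list program, and a possible imbalance of up to 4 per list instead of 2.
3. **If enrolment has closed, as the dates imply,** leave blocks of four as the record of what was done. Before database lock, add to SAP 8.5 a sensitivity analysis of the primary flare comparison adjusted for the probability of MMF given earlier allocations in the block (reverse propensity score). Under blocks of four this takes the values 0, 1/3, 1/2, 2/3 or 1. Report baseline SLEDAI-2000 by that probability, and compute it from the actual list structure. Cost: one extra analysis using the list, the enrolment order and data already planned. Its power to detect steering is limited, so a null result would not prove that none occurred.
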